## Procedure for accounting for any missing data

If missing data are present in the computerized database, we will first check the original records to attempt to complete those variables. In the analyses, we will use multiple imputation^26^ with 10 imputed datasets to replace missing values on outcome and predictor variables (using the *mice*/*Hmisc* package in R) and combine the results using Rubin’s rules^27^. If 10 imputed datasets are not sufficient to ensure stability of estimates, we will use 20 imputed datasets. The imputation predictors will include HbA1c at baseline, 6-months and 9-months; weight; age; and sex. Multiple imputation makes maximum use of available data and maximizes statistical power while requiring less strict theoretical assumptions than to a complete case analysis, or single imputation of mean values; this is a standard method for analysing clinical trials data ^28^.

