# Study Design

This study is a randomized controlled trial in adults aged 30-70 (at enrolment) with newly diagnosed type 2 diabetes over the study period of Jan 2020 to Dec 2022. We plan to enrol 261 adults and follow them for 9-months (6-month intervention period and a 3-month post-intervention follow-up period) to assess glycaemic control and other health indicators. A meta-analyses of clinical trials show a pooled difference of -0.6 percentage points in HbA1c after a minimum 8-12 weeks of exercise intervention ^12,13^. Consequently, the 6-month intervention period is designed to be sufficient to assess changes in lifestyle, but not of excess duration in order to reduce participant drop-out and loss to follow-up. If a 6-month trial of lifestyle intervention fails to adequately control blood glucose level, it may be appropriate to consider additional medication for glycaemic control ^4–6^.

Participants will be randomly assigned to one of three groups (in ratio 1:1:1): arm A (financial incentives in addition to standard care), arm B (financial and social incentives in addition to standard care), and arm C (control arm receiving standard care). All participants will establish a baseline step count of physical activity using the second week of recorded measurements. The first week of recorded measurements will be ignored to minimise the potential upward bias from elevated physical activity during initial device use. Subsequently, all participants will receive weekly increases of 1,000 daily step targets from their baseline levels to a maximum target of 10,000 steps per day (depending on age, physical condition, physician guidance). The 10,000-step target approximates the 30 minutes of daily exercise recommended by the American College of Sports Medicine ^14^. We will impute daily values less than 1,000 steps as these values are unlikely to represent actual activity ^15,16^. Participants will use their smartphones to track step counts on the same pre-specified activity tracking app for consistency. Although smartphones are expensive, smartphone penetration in Hong Kong is very high, at above 88% of the population aged 10 or above in 2017 ^17^. All participants will be provided with a pedometer to account for physical activity. Participants are followed for an additional 3-months after the cessation of incentives to assess any continued effects and the sustainability of lifestyle change.

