## Secondary outcomes

The secondary outcome measures at 6-months and 9-months include:

- proportion of participants with good/excellent diabetes control (HbA1c threshold ≤7% & ≤6.5%)
- change in body weight and body mass index
- changes in lipid profile (HDL- and LDL-cholesterol) and blood pressure
- proportion of participants requiring initiation of additional medication or higher dose adjustment for glycaemic control
- proportion of smokers quitting
- change in level of physical activity (step count)
- change in health care attendances and admissions

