# Statistical analysis

## Statistical methods

We compare sample characteristics between the arms using ANOVA for continuous variables, and Kruskal-Wallis test for categorical variables. The change from baseline HbA1c will be calculated for each individual participant. The time-matched change from baseline data will be analysed by a repeated-measure analysis of covariance (ANCOVA), fitting terms appropriate to the study design, including treatment group, time and group-by-time interaction. Participants will be included in the model as a random effect. Baseline values will be included as a covariate in the above models. Interim analysis will be performed after ~50% participants having completed the study. We will use the bootstrap method to resample participant groups 200 times to calculate the 95% confidence intervals. As a sensitivity analysis, we will use per protocol analysis to check for the robustness of our results. All analyses will be conducted using R statistical software.

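### The single imputation predictor list names none of the lipid, blood pressure or step-count values, so if followed as written it costs precision on those secondary comparisons

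*Protocol*

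**What the plan says.** Under Procedure for accounting for any missing data, the protocol plans 10 imputed datasets (20 if estimates are unstable) "to replace missing values on outcome and predictor variables", combined by Rubin's rules. The same paragraph names the predictors: "The imputation predictors will include HbA1c at baseline, 6-months and 9-months; weight; age; and sex". It prefers imputation to complete cases on the ground that imputation uses the data fully and gives the most power. No other predictor list appears in the protocol.

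Secondary outcomes, assessed at 6 and 9 months, include "changes in lipid profile (HDL- and LDL-cholesterol) and blood pressure" and "change in level of physical activity (step count"). None of these variables is in the list at any visit. Weight is in the list, without visits. Statistical methods adds: "Baseline values will be included as a covariate in the above models".

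Study Design has a separate rule for low step counts: "We will impute daily values less than 1,000 steps as these values are unlikely to represent actual activity". It gives no method or predictors, and it concerns implausible daily readings rather than a participant with no 6-month step outcome.

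**The concern.** For most continuous measurements, the best predictor of a participant's follow-up value is that participant's own baseline. It is also the value from which the change is taken and, if the models in Statistical methods are used for the secondary outcomes too, the covariate in the analysis model. An imputation model that leaves it out fills the gaps with values almost unrelated to baseline. The fitted baseline-to-follow-up slope is pulled toward zero, residual variance rises, and the standard error of the arm comparison grows.

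The analysis is by intention to treat with all randomized participants, so every dropout's lipid, blood pressure and step-count outcome would come from this model. Someone lost before 6 months has no follow-up HbA1c either. Baseline HbA1c, weight, age and sex would then be all that informs, say, their LDL.

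At stake is the precision of several secondary comparisons and, under one particular pattern of dropout, their bias.

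**Working it through.** **Inputs from the protocol.** 87 participants per arm. Dropout is 10% in Randomization and in Sample size justification (87 × 0.9 = 78.3, so 78 per arm). Figure 1 shows 13 lost per arm (13/87 = 14.9%, leaving 74). Both are used as the range. The protocol gives no figure for the performance of the imputation, so there is none to reproduce.

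**Assumptions, not in the protocol.** Correlation ρ between an outcome's baseline and follow-up: 0.5 to 0.8. The listed predictors, summarised as one variable, correlate 0.2 with the outcome's baseline. True arm effect: 0.40 SD.

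**Method.** Simulation of two arms of 87: 800 replicates, normal-linear imputation with 10 datasets, ANCOVA on own baseline, Rubin's rules. Treatment arm is in both imputation models, so that only the missing own baseline is tested. In the table, missingness depends on baseline equally in both arms. The complete-case column is the approximation √(2(1−ρ²)/n) with n = 78 or 74; for example √(2 × 0.36/74) = 0.099.

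| ρ | Missing | SE, list + arm | SE, list + arm + own baseline | Ratio | SE, complete cases |
|---|---|---|---|---|---|
| 0.5 | 10% | 0.147 | 0.140 | 1.05 | 0.139 |
| 0.5 | 15% | 0.154 | 0.144 | 1.07 | 0.142 |
| 0.8 | 10% | 0.120 | 0.097 | 1.24 | 0.096 |
| 0.8 | 15% | 0.131 | 0.100 | 1.31 | 0.099 |

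A repeat of the simulation put the smallest excess at about 4%, hence the range of 4% to 31%. A further run at ρ = 0.7 and 15% missing, with the listed predictors unrelated to the outcome, gave 0.140 against 0.119 (18% wider) and 0.116 for complete cases.

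**Mechanism.** In imputed records the slope on own baseline is about ρ × 0.2² = 0.04ρ. With ρ = 0.8 and 15% missing, the overall slope is about 0.85 × 0.8 + 0.15 × 0.032 = 0.685 instead of 0.8.

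**How much is real loss.** The spread of the estimates across replicates grows less than the Rubin's-rules SE. In table order it is 0.141 v 0.137, 0.150 v 0.144, 0.107 v 0.094 and 0.116 v 0.100, which is 3%, 4%, 14% and 16%. The rest is overstated uncertainty from an imputation model poorer than the analysis model. Statistical methods also plans bootstrap confidence intervals. If those are the ones reported, the smaller figures are probably the better guide to interval width.

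**Bias.**
- Missingness depends on baseline equally in both arms: estimates 0.39 to 0.40 against a true 0.40, so essentially none.
- In one arm only (separate run): bias 0.06 to 0.10 SD.
- In opposite directions by arm: estimates 0.50 to 0.60, so bias 0.10 to 0.20 SD. With own baseline added they return to 0.39 to 0.41.

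**Not computed.** The simulation covers continuous outcomes only, not medication initiation, smoking or health care attendances. It adds own baseline but not the other follow-up visit, so any further gain from that visit is not quantified.

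**The case against.** The strongest reply is that the list is open. It says what the predictors will include, not that nothing else may be used. Statistical methods names only HbA1c as the outcome analysed, so the list can be read as the primary-outcome model, with other outcomes left to a statistical analysis plan that is not at hand. Discarding a participant's own LDL would also sit badly with the section's aim of using the data fully.

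Much of this stands. A reader might infer that lipids, blood pressure and step counts will definitely be imputed without their own values. The protocol does not say so. What it does is extend imputation to outcomes generally, give one list, and spell out visits for HbA1c alone. An analyst could follow that to the letter, and the result would defeat the section's stated reason for imputing.

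A reader might also infer that the secondary results will be biased. That needs dropout related to the outcome's baseline differently by arm. The arms do differ in feedback and in money at risk, so such a pattern is conceivable for step count, but the protocol gives no evidence for it.

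Three further limits are fair:
- Medication initiation is a binary event during follow-up ("proportion of participants requiring initiation of additional medication or higher dose adjustment for glycaemic control"), so own baseline can only mean baseline medication use.
- The correlations are assumed, and at 10% missing and ρ = 0.5 the loss is small.
- Imputation with own baseline does not beat complete cases here either (0.119 v 0.116 at ρ = 0.7). The point is that imputation without it does clearly worse when the correlation is high.

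**Conclusion.** The point holds conditionally. The named list omits the own baseline and other-visit values of HDL, LDL, blood pressure and step count. If it is applied as written, the Rubin's-rules standard error of these comparisons is about 4% to 31% wider than with own baseline added, and no better than complete cases. That range rests on assumed correlations of 0.5 to 0.8, 10% to 15% missing, and listed predictors only weakly related to the outcome.

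Bias is a possibility under arm-specific, baseline-dependent dropout and should not be presented as expected. The primary HbA1c outcome and the HbA1c-threshold proportions are not affected by this omission, because HbA1c is listed at every visit. The point is a free improvement to the secondary analyses and does not threaten the trial's main conclusion.

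**What to change.** Keep the existing list and add to it:

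> Each outcome is imputed from its own available baseline, 6-month and 9-month values and treatment arm, with HbA1c, weight, age and sex retained as auxiliary predictors; for medication change, baseline medication use is included.

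Treatment arm belongs in the sentence because the present list does not name it either. In the same simulation, leaving arm out shrank a 0.40 SD effect to 0.34 to 0.36 even with own baseline included, so adding own values alone would leave that problem in place.

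The cost is a few lines of *mice* code and a slightly larger imputation model. No new data are needed, since analysing changes at 6 and 9 months already requires these values.

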## Procedure for reporting any deviations from the original statistical plan

Any deviations from the original statistical plan will be described and justified in the final report.

## Selection of participants to be included in the analyses

We will follow an intention-to-treat approach in the analyses; therefore all randomized participants will be included.

## Sample size justification

We propose to enrol 261 participants into our study. Based on published meta-analyses of clinical trials on the effect of lifestyle modification (diet and exercise interventions), we assume a mean difference of -0.6 in HbA1c with a standard deviation for each group of 1.5 percentage points.^12,13^ A sample size of 234 subjects (78 per group) will achieve 80% power to reject the null hypothesis of equal means between any two groups. The calculation is based on equal-variance t-test with a significance level of 0.05. We allow for a 10% dropout rate, giving the total target sample size of 261 (87 per group). Interim analysis will be performed after ~50% participants having completed the study. Sample size re-estimation may be applied based on interim look results upon the advice of our biostatistician. ​

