## Randomization

The random allocation process will be concealed from the front-line team, using tamper-proof methods, by way of pre-assignment based on a computer-generated sequence of random numbers administered by an independent research assistant. A sequence of random numbers will be generated prior to the start of the study by a statistician. To avoid baseline unbalance, we will stratify the randomization by age (30-49, 50-70) and sex. Computer software (R) will be used to generate the randomization sequence, using a block randomization structure with block sizes of 6 for the enrolment of participants.

The study will remain blind to laboratory and analysis staff. Research staff members at the designated study clinics who had no access to the randomization sequence will allocate a unique code to each of the participants based on their order of attendance. Because the allocation process will be concealed, the identity of the intervention groups will be unknown to the laboratory staff. The randomization codes will be masked from those assessing the outcomes and will only be revealed to the investigators after completion of the follow-up. A study statistician, uninvolved with other trial activities, will have access to the randomization codes for the purpose of conducting regular interim analyses and safety monitoring.

We will enrol 261 participants and randomly allocate each participant to one of the three study arms in equal proportion (1:1:1 ratio) (Figure 1). We assume 10% of participants do not complete the intervention or are lost to follow-up.

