**Figure 1. CONSORT Flow Diagram**

Discontinued or Lost to follow-up (n=13)

Analysed (n=74)

Analysed (n=74)

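### The stated 80% power at 78 per group holds only for an undeclared one-sided 0.05 test; two-sided it is about 70%, and about 68% at the 74 per arm in Figure 1

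*Protocol*

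**What the plan says.** Under *Sample size justification* the Protocol gives its effect assumption: "we assume a mean difference of -0.6 in HbA1c with a standard deviation for each group of 1.5 percentage points". It then states the result, claimed for every pairwise comparison of arms: "A sample size of 234 subjects (78 per group) will achieve 80% power to reject the null hypothesis of equal means". The method is named in the next sentence: "The calculation is based on equal-variance t-test with a significance level of 0.05". Whether that level is one-sided or two-sided is not said there or anywhere else in the Protocol. The same section inflates 78 to 87 per group (261 in total) for 10% dropout.

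The *Randomization* section repeats the loss assumption: "We assume 10% of participants do not complete the intervention or are lost to follow-up". Figure 1 (CONSORT flow diagram) has different numbers. In each of the three arms 87 are allocated, 13 are discontinued or lost, and 74 are analysed.

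*Statistical methods* plans a repeated-measures ANCOVA on change from baseline HbA1c, with the baseline value as covariate, and bootstrap resampling "to calculate the 95% confidence intervals". The analysis population is intention to treat, with multiple imputation of missing values.

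**The concern.** The inputs give a standardised difference of 0.6/1.5 = 0.40. At that effect size 78 per group looks too few for 80% power with a conventional two-sided 0.05 t-test, and looks like the answer to a one-sided calculation. Separately, the flow diagram plans to analyse fewer participants per arm than the calculation requires.

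This section is the only justification for the trial's size on its primary outcome. If the power is overstated, the chance of missing a real 0.6-point difference under the stated test is about 30% rather than 20%, and a null result could be read as stronger evidence against incentives than it is. An ethics committee, funder or journal can recompute the figure in a minute.

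**Working it through.** **Inputs** (all from *Sample size justification* unless noted)

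- Difference δ = 0.6, SD σ = 1.5, so d = 0.40
- Equal-variance two-sample t-test, α = 0.05, sidedness not stated
- n = 78 per group, claimed power 80%
- 10% dropout, 87 per group enrolled
- 74 per arm analysed, 13 per arm lost (Figure 1)

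**Formula.** Noncentrality λ = δ / (σ√(2/n)), with 2n − 2 degrees of freedom. Power is the probability that a noncentral t variable with that λ exceeds the critical value t(1−α) for a one-sided test or t(1−α/2) for a two-sided test; the opposite tail is negligible here.

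**Step 1: reproduce the stated figure.** At n = 78, λ = 0.6 / (1.5 × √(2/78)) = 2.498, with 154 degrees of freedom.

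- One-sided 0.05: critical value 1.655, power **80.0%**. The smallest n giving 80% is exactly 78.
- Two-sided 0.05: critical value 1.975, power **69.9%**. The smallest n giving 80% is 100 (99 by the normal approximation).

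The exact match at 78 indicates that a one-sided level was used without being declared.

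**Step 2: power at the sample sizes the Protocol mentions.**

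| n per arm | Source | One-sided 0.05 | Two-sided 0.05 |
|---|---|---|---|
| 74 | analysed in Figure 1 | 78.1% | 67.6% |
| 78 | sample size section | 80.0% | 69.9% |
| 87 | all randomised, no information lost | 83.7% | 74.6% |
| 100 | needed for 80% two-sided | 88.0% | 80.4% |

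**Step 3: detectable difference.** With 78 per arm and 80% two-sided power, the detectable difference is 0.68 (0.677), not 0.6.

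**Step 4: attrition.** 78/0.90 = 86.7, so 87 per group, and 3 × 87 = 261; the text is consistent with itself. Figure 1 has 13/87 = 14.9% lost and 87 − 13 = 74 analysed, four below the 78 required. A 10% loss from 87 would be about 9, leaving 78.

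**Step 5: would another reading rescue 80%?**

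- *Three-group ANOVA F-test at 78 per group:* 60% to 73%, depending on where the middle mean lies.
- *Both incentive arms pooled against control (2:1):* about 82% two-sided, but the section claims power for any pair of groups.
- *Multiplicity adjustment of the pairwise tests:* lower still, about 59% at 0.025 and 53% at 0.0167.
- *Baseline-adjusted ANCOVA,* a simplified single-time-point version with residual SD = σ√(1 − r²), assuming 1.5 is the SD of HbA1c values and r is the correlation between baseline and follow-up: at 78 per group, two-sided, 74% (r = 0.3), 77% (r = 0.4) and 82% (r = 0.5). The Protocol gives no r.

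**The case against.** The best case for the Protocol has three parts.

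**Sidedness is inferred.** The effect is written with a sign, the 80% is exactly right one-sided, and the 95% intervals are not tied to a decision rule. The strictly provable defect is therefore an undeclared one-sided level. That is fair, but it does not save the text. The claim covers every pair of groups, including arm A against arm B, for which the Protocol states no direction. The primary objective is also undirected. A one-sided 0.05 test does not correspond to a 95% two-sided interval. And at the 74 per arm in Figure 1, even the one-sided power is 78.1%.

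**The t-test is not the planned analysis.** The trial will use a baseline-adjusted repeated-measures model, which can have more power. The Protocol does not say whether 1.5 is the SD of HbA1c values or of change. If it is the SD of change, with equal variances at both times, ANCOVA power at 78 per group is 87%, 82% and 77% for r = 0.3, 0.5 and 0.7. This part stands as a qualification: the 30% type II risk belongs to the stated t-test, and the power of the planned analysis is simply not given. It does not make the stated t-test figure correct.

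**Intention to treat includes all 87.** Multiple imputation does keep everyone in the analysis, so 67.6% is not necessarily the power of the final analysis. But imputation does not restore the missing information in full, and even complete data on 87 per arm give only 74.6% two-sided.

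The section also says that sample size re-estimation may follow the interim look. That is discretionary and does not correct the stated figure.

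**Conclusion.** The concern holds. For the test the Protocol names, 78 per group gives 80% power only one-sided. On the two-sided reading that its equal-means null and 95% intervals imply, power is 69.9%, about ten percentage points short. The conflict between 10% loss in the text and 14.9% in Figure 1 is a separate and certain error. It lowers power by about two further points and takes it below 80% on either reading.

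The conclusion rests on the Protocol's own difference, SD, test and level, and on a two-sided test being intended. It does not establish the power of the planned ANCOVA, which depends on a correlation and a definition of the SD that the Protocol does not supply.

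**What to change.** In *Sample size justification*:

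1. State that the test is two-sided at 0.05.
2. Choose one of these:
   - Replace the 80% claim with about 70% power for a difference of 0.6, equivalent to 80% power for 0.68, with 78 per group.
   - Restate power for the baseline-adjusted ANCOVA. Say whether 1.5 is the SD of HbA1c values or of change, and declare and justify the assumed correlation. If it is the SD of values, r must be close to 0.5 to support 80% at 78 per group.
   - Keep 80% for 0.6 by t-test. This needs 100 evaluable per group: 100/0.90 = 111.1, so 112 enrolled per group and 336 in total.
3. If a one-sided test really was intended, say so, justify it for each pair of arms, and align the confidence intervals with it.

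Use one dropout figure throughout. Either correct Figure 1 to 9 lost and 78 completing per arm, or change the text to 15% and 74 and give the power at 74. Also make clear how the flow diagram's analysed number fits with intention to treat, which includes all 87.

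The first two options in item 2 cost one reworded paragraph and a corrected figure, with no added enrolment. The price is a less favourable power statement, or an explicit assumption that has to be defended.

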## Primary objective

- To investigate the effect of financial and social incentives based on behavioural economic principles on glycaemic control at 6-months for people with newly diagnosed type 2 diabetes.

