Arm A (financial incentives): Participants will receive the usual standard care (same as control group), a loss-framed financial incentive, and weekly feedback on performance for 6 months.

Arm B (financial and social incentives): Participants will receive the usual standard care (same as control group), a loss-framed financial incentive, social incentives, and weekly feedback on performance for 6 months.

Arm C (control): Participants will receive standard care under the risk factor assessment and management programme (RAMP) including patient screening and education on diet, physical activity, and smoking conducted by a multi-disciplinary team ^18^.

The study will last for a total of 36 months including a 11-month suspension due to COVID-19 pandemic. This includes a 11-month recruitment period on rolling basis, 9-month follow-up period for each participant (consisting of 6-months intervention period and 3-month post-intervention period) and 3-month buffer for any rescheduling of follow-up. We plan to allow 4-months for the data analysis and 3-months to write-up our findings.

The pragmatic study design is based on the PRECIS-2 tool (Appendix 3) and RE-AIM frameworks.^19,20^ This trial is registered at ClinicalTrials.gov and will follow this pre-specified protocol.

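### The 80% power claimed between any two groups has no stated basis for arm B against arm A, and at a difference of 0.6 it needs a one-sided test that the protocol does not declare

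*Protocol*

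**What the plan says.** Under Sample size justification the protocol writes: "we assume a mean difference of -0.6 in HbA1c with a standard deviation for each group of 1.5 percentage points". From this it derives 234 evaluable participants, 78 per group, and says that this number "will achieve 80% power to reject the null hypothesis of equal means between any two groups". On the test it says only: "The calculation is based on equal-variance t-test with a significance level of 0.05". A 10% dropout allowance then gives 87 per group, 261 in all.

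The same section attributes the -0.6 to meta-analyses of diet and exercise interventions. The Study Design section, citing the same two references, describes it as a "pooled difference of -0.6 percentage points in HbA1c after a minimum 8-12 weeks of exercise intervention".

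The trial has three arms. Arm C gets standard care. Arm A adds a loss-framed account and weekly feedback. Arm B gets standard care with "a loss-framed financial incentive, social incentives, and weekly feedback on performance for 6 months". Interventions to be Administered defines the social part as peer comparison and support from a nominated person. The primary objective is "To investigate the effect of financial and social incentives based on behavioural economic principles on glycaemic control at 6-months"; it names no pairwise contrast.

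**The concern.** In a three-arm trial, any two groups means A v C, B v C and B v A. An effect of a lifestyle intervention against control can at most inform the first two. In B v A both arms carry the same financial incentive and feedback, so the expected difference is only what the social incentives add. The protocol neither states nor justifies a figure for that increment, yet it attaches 80% power to the contrast.

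B v A is the only contrast that isolates the social incentives, since they are all that separates the two arms. A reader who trusts the printed 80% could take a non-significant B v A result as good evidence that social incentives add nothing. If the increment is only part of -0.6, such a result would be quite likely even when the incentives help.

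**Working it through.** **Inputs**

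- Difference 0.6, SD 1.5, alpha 0.05, equal-variance t-test, 78 per group, 10% dropout: Protocol, Sample size justification.
- Content of the arms: Protocol, Study Design and Interventions to be Administered.
- Sidedness: not stated, so both readings are shown.
- B v A difference: not stated. Increments of 0.15, 0.3 and 0.45 are assumptions. They are one quarter, one half and three quarters of the cited effect.

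**1. The protocol's own figure**

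n per group = 2 × (z for alpha + z for power)² × SD² / difference².

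- One-sided 0.05: 2 × (1.645 + 0.842)² × 1.5² / 0.6² = 77.3, rounded up to 78. This reproduces the protocol; noncentral-t power at 78 is 80.0%.
- Two-sided 0.05: 2 × (1.960 + 0.842)² × 1.5² / 0.6² = 98.1, rounded up to 99 (100 with the exact t). This does not reproduce it; noncentral-t power at 78 is 69.9%.
- Dropout: 78 / 0.90 = 86.7, rounded up to 87; 3 × 87 = 261. This reproduces.

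**2. Can one difference serve all three pairs?**

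(B − C) = (A − C) + (B − A). Take the arms in the order C, A, B.

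- If A − C and B − C are both -0.6, then B − A = 0.
- If A − C and B − A are both -0.6, then B − C = -1.2, twice the cited effect.
- If B − C = -0.6 and A lies between, then A − C and B − A share the -0.6, and neither can reach it unless the other is zero.

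Every pair can therefore have at least the stated power only if B v C is at least -1.2. The protocol neither states nor supports a figure of that size.

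**3. Power for B v A at 78 per group**

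Standard error = 1.5 × √(2/78) = 0.240. Noncentrality = difference / 0.240, with 154 degrees of freedom.

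| B v A difference | Noncentrality | Power, two-sided 0.05 | Power, one-sided 0.05 |
| --- | --- | --- | --- |
| 0.15 | 0.62 | 9.5% | 15.3% |
| 0.30 | 1.25 | 23.7% | 34.4% |
| 0.45 | 1.87 | 46.1% | 58.7% |
| 0.60 | 2.50 | 69.9% | 80.0% |

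If B − C is held at -0.6, the same rows read in reverse give A v C: a B v A increment of 0.45 leaves A v C at 0.15, and so on.

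**4. Precision**

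95% CI half-width for B v A = 1.975 × 0.240 = 0.47 points, wider than each of the three assumed increments.

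**5. What 80% would take at an increment of 0.3**

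By the formula in step 1 with 0.3 in place of 0.6: 310 per group one-sided, 393 two-sided.

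**The case against.** The best defence is that the power statement is conditional: if two groups differ by 0.6 with SD 1.5, the t-test has the stated power whichever two they are. It does not assert that all three pairs differ by 0.6 at once. This is right as to form, and it rules out a stronger reading that a reader might infer, namely that the claim is arithmetically impossible. Means of 0, -0.6 and -1.2 would satisfy it. But a sample size justification has to justify the difference for each contrast it says is powered, and for B v A nothing is offered.

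It is also fair that the objectives do not single out B v A, that no contrasts are listed under Statistical methods, and that nothing in the protocol says a non-significant B v A result would be read as no benefit. The misreading is a risk created by the wording, not a stated plan. The ranking of contrasts can be left to the SAP, but the power claim itself is printed in the protocol.

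The planned analysis is a repeated-measures ANCOVA with baseline as covariate, which may be more precise than the unadjusted t-test used here. At an increment of 0.3, however, 80% two-sided power with 78 per group would need the residual SD to fall from 1.5 to 1.5 × √(78/393) = 0.67. Counting all 87 randomised per group as complete gives only 26% two-sided or 37% one-sided at 0.3. The possible sample size re-estimation names no contrast, so it cannot be counted on to repair this one.

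**Conclusion.** The point stands: the 80% is unsupported for B v A. If the social increment is 0.15 to 0.45 points, B v A power is about 10% to 46% two-sided or 15% to 59% one-sided. Separately, the 80% holds for a difference of 0.6 only with an undeclared one-sided test; two-sided it is about 70%, and this affects every contrast.

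These figures rest on the protocol's SD of 1.5, 78 per group and an unadjusted t-test. The increments are assumptions, because the protocol gives none.

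Two further readings go beyond the documents. One is a single power range for B v A such as 5% to 34%. Its lower end is the type I error at no difference rather than power, and its upper end combines a one-sided test with an increment capped at 0.3. The other is a shortfall of at least 46 points: at an increment of 0.45 the one-sided shortfall is about 80 − 59 = 21 points. What the documents do support is that no B v A effect is given to justify the claim.

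**What to change.** In Sample size justification:

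1. Replace the reference to any two groups by each incentive arm against control (A v C, B v C), worded as power to detect a difference of 0.6 in each contrast taken separately. This avoids implying that both differences equal -0.6, which would make B v A zero.
2. State whether the test is one- or two-sided and give the matching power at 78 per group: 80% one-sided or about 70% two-sided.
3. State that B v A is not powered. Give its power over a range of assumed increments (for example 0.15, 0.3 and 0.45, labelled as assumptions) and its expected 95% CI half-width of about 0.47.
4. Say that B v A will be reported as an estimate with its 95% CI, and that a non-significant result will not be read as no added benefit of social incentives.

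The cost is a few sentences. There are no extra participants, visits or data. The downside is that the stated power becomes less favourable: openly low for B v A and, if the test is two-sided, about 70% for the contrasts against control.
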